## Abstract

**Background:**

While there is convincing evidence on interventions to improve bowel preparation for patients, the evidence on how to implement these evidence-based practices (EBPs) in outpatient colonoscopy settings is less certain. The Strategies to Improve Colonoscopy (STIC) study compares the effect of two implementation strategies, physician education alone versus physician education plus an implementation toolkit for staff, on adoption of three EBPs (split-dosing of bowel preparation, low-literacy education, teach-back) to improve pre-procedure and intra-procedure quality measures. The implementation toolkit contains a staff education module, website containing tools to support staff in delivering EBPs, tailored patient education materials, and brief consultation with staff to determine how the EBPs can be integrated into the existing workflow. Given adaptations to the implementation plan and intentional flexibility in the delivery of the EBPs, we utilize a pragmatic study to balance external validity with demonstrating effectiveness of the implementation strategies.

**Methods/Design:**

Participants will include all outpatient colonoscopy physicians, staff, and patients from a convenience sample of six endoscopy settings. Aim #1 will explore the relative effect of two strategies to implement patient-level EBPs on adoption and clinical quality outcomes. We will assess the change in level and trends of clinical quality outcomes (i.e., adequacy of bowel preparation, adenoma detection) using segmented regression analysis of interrupted time series data with two groups (intervention and delayed start). Aim #2 will examine the influence of organizational readiness to change on EBP implementation. We use a PRECIS diagram to reflect the extent to which each indicator of the study was pragmatic versus explanatory, revealing a largely pragmatic study.

**Discussion:**

Implementation challenges have already motivated several adaptations to the original plan, reflecting the nature of implementation in real-world healthcare settings. The pragmatic study responds to the evolving needs of its healthcare partners and allows for flexibility in intervention delivery, thereby informing clinical decision-making in real-world settings. The current study will provide information about *what* works (intervention effectiveness), *for whom* it works (influence of Medicaid versus other insurance), in *which contexts* it works (setting characteristics that influence implementation), and *how* it works best (comparison of implementation strategies).

**Electronic supplementary material:**

The online version of this article (doi:10.1186/s13012-015-0276-3) contains supplementary material, which is available to authorized users.

## Background

In 2002, more than 14 million colonoscopies were performed in the United States of America [1] and annual procedures are on the rise [2] due to increased physician recommendation [3, 4] and patient preferences for colonoscopy, over fecal occult blood test or sigmoidoscopy for colorectal cancer screening [2]. Inadequate bowel preparation and substantial variability in adenoma detection [5–7] from 7.5 to 33.3 % [6, 8] are critical colonoscopy quality issues [5]. To improve the quality of colonoscopy, the American Society for Gastrointestinal Endoscopy and the American College of Gastroenterology recommend that for asymptomatic patients more than 50 years of age, adenoma detection should be >30 % for men and >20 % for women [5, 9], and inadequate bowel preparation should be <15 % [10, 11]. Inadequate bowel preparation is a primary cause of low adenoma detection [12] and can occur in over 30 % of patients, or 4.2 million persons per year [13]. In addition, inadequate bowel preparation increases complication rates [14] and cost of colonoscopy by 12–22 % [12]. Patients’ age, sex, and comorbidities are associated with adequacy of bowel preparation [6]. However, Medicaid insurance is among the strongest risk factors for inadequate bowel preparation (odds ratios 1.846–8.707 compared to other insurance). Given that only 39 % of Medicaid-insured adults read at or above an 8th grade level, low-literacy education for bowel preparation might be particularly beneficial to the quality of colonoscopy for patients insured by Medicaid [15].

Despite these grim statistics, randomized controlled trials of two interventions (one clinical and one behavioral) hold promise for improving bowel preparation and adenoma detection. Irrespective of the bowel preparation [16], *split-dosing* can improve the adequacy of bowel preparation by 10 percentage points (*p* < 0.0001) and adenoma detection by six percentage points (*p* < 0.001) and is more highly accepted [17] by patients compared to taking a full dose on the same day [18–20]. In addition, an almost fourfold improvement in adequacy of bowel preparation has been found among patients who receive *low-literacy education* compared to education written for 6th grade or higher [21]. However, written instructions are more effective when combined with verbal instructions [18, 22], signaling the importance of confirming patient understanding of bowel preparation instructions. Representing a third evidence-based practice (EBP) for improving bowel preparation, *teach-back* is the practice of reviewing instructions with patients, ensuring that patients can repeat key points (i.e., teach back), and addressing any barriers to completion of instructions. Both low-literacy education and teach-back are in accordance with the Agency for Healthcare Research and Quality’s and the National Quality Council’s recommendation for using universal precautions to improve health literacy in all patients.

While there is convincing evidence on interventions to improve bowel preparation for patients, the evidence on how to implement these patient interventions in outpatient colonoscopy settings is less obvious. Outpatient colonoscopy requires relationship-centered care [23] where staff provides patients with education for bowel preparation that reflects the physician’s choice of bowel preparation medication and dose to maximize the potential for a clean colon on the day of the procedure. The structure and qualities of the physician-staff relationship for outpatient colonoscopy remain unstudied. Yet understanding the qualities and patterns of these relationships can inform the implementation of changes to patient procedures to improve bowel preparation prior to outpatient colonoscopy [23]. Our study fills this research gap in a pragmatic study that examines the effect of implementation strategies directed toward physicians and staff in endoscopy settings on implementation of EBPs to improve bowel preparation for patients overall and for those insured by Medicaid. We also leverage the pragmatic study to conduct formative research about theory-informed aspects of endoscopy settings (e.g., readiness to change) that influence implementation of patient interventions. These healthcare quality and implementation issues are of critical importance to decision-makers in health service organizations because practice-based stakeholders are under increased pressure by Medicare and Medicaid to improve quality of care and reduce cost.

Addressing barriers to implementation of EBPs for bowel preparation can help reduce the substantial variation in colonoscopy outcomes found across healthcare settings. Several frameworks of implementation for interventions to improve health have emerged over the last decade [24, 25]. The Promoting Action on Research Implementation in Health Services (PARIHS) framework is among the most researched frameworks of implementation [26]. There is evidence to suggest that key factors of the PARIHS framework—perceptions of the evidence, context, and facilitation—are critical precursors to successful implementation of complex changes in healthcare settings (Fig. 1) [27, 24]. Two aspects of scientific evidence, relative advantage of the new intervention over an existing intervention [27] and compatibility with existing values and past experiences, are strongly correlated with adoption of interventions [28, 29]. Context refers to organizational culture and leadership [29, 25]. These contextual factors affect staffs’ capacity to facilitate implementation by encouraging analytical engagement in quality improvement processes [30]. Facilitation refers to the structures and processes in place to support change in clinical practice [29, 31]. When implementation efforts are interdependent across multiple levels of healthcare providers, as is expected in this study, context and facilitation are highly influenced by the structure and quality of the physician-staff relationship. As informed by leader-member exchange (LMX) theory, employees (i.e., staff) and supervisors (i.e., physicians) establish unique exchange relationships that contribute to employee work attitudes and performance (i.e., implementation of evidence-based colonoscopy care) [32]. Together, evidence, context, and facilitation contribute to organizations’ readiness to successfully implement change [24, 31]. Published reports on complex change initiatives suggest a median implementation success rate of only 33 % [24] due to factors such as false start of an intervention, staff resistance to implementation, or failure to implement an intervention [27]. Understanding the structure and quality of relationships between the physicians and implementers of patient education in endoscopy settings is important to developing strategies to increase adoption of EBPs. Our study 1) compares the effect of two implementation strategies on the adoption of EBPs to improve patient bowel preparation and 2) examines whether physician-team level aspects of readiness to change are associated with colonoscopy quality, patient, and implementation outcomes to gain a better understanding of the nature of implementation of pre-colonoscopy patient interventions in endoscopy settings.

**Fig. 1 Fig1:**
[figure not shown]
Conceptual model of STIC study. Adapted from the Proctor et al. conceptual model of implementation research [36, 37]

### Present study

The Strategies to Improve Colonoscopy (STIC) study compares the effect of two implementation strategies, physician education alone versus physician education *plus* an implementation toolkit for staff (i.e., education, website, tailored patient education materials, and a brief consultation), on adoption of three EBPs to improve pre-procedure quality measures (patient experience, adequacy of bowel preparation) and intra-procedure quality measures (cecal intubation, adenoma detection). The EBPs are as follows: 1) split-dosing of bowel preparation, 2) low-literacy education, and 3) teach-back. The goal of the physician education is to improve perceptions of the EBPs and to motivate change among physicians [33], whereas the goal of the implementation toolkit is to improve perceptions of the EBPs, motivate change, and *enable change* among staff [30]. The toolkit will assist endoscopy staff to implement the three EBPs to improve education for bowel preparation for patients. The implementation toolkit contains 1) staff education module, 2) a website containing tools to support staff in learning teach-back and providing low-literacy education materials for patients, 3) patient education materials including a 5-month supply of printed patient education brochures tailored to their site and bowel preparation preferences, and a laminated pocket card and poster to remind and help staff to use teach-back, and 4) a brief consultation with study staff to determine how the EBPs can be integrated into the existing workflow. Education alone is a weak strategy to change physician behavior [34, 35], and there is limited evidence on the effect of implementation toolkits on staff implementation of EBPs. Therefore, the STIC study aims to test the effect of physician education versus physician education plus an implementation toolkit for staff on the implementation and quality outcomes. In light of several adaptations made to the implementation plan and the intentional flexibility in the delivery of the EBPs, this study utilizes a pragmatic study to balance external validity with demonstrated effectiveness of the implementation strategies.

## Methods/Design

### Strategic partners

Our strategic partners include physician champions from six endoscopy settings in the St. Louis area. All settings are affiliated with BJC HealthCare, one of the largest non-profit healthcare organizations in the United States of America with 13 hospitals. Despite the affiliation, each hospital is run as a separate organization. Quality improvement initiatives are not routinely implemented across BJC. However, BJC has a Center for Clinical Excellence that provides decision support, analytic teams, and performance improvement services to affiliated hospitals, and they have a strong interest in learning how to implement widespread change throughout BJC to improve quality of care. Two of the settings are teaching hospitals where colonoscopies are performed by physicians from the university. At two other partnering hospitals, colonoscopies are performed by physicians in private practice.

### Study overview

We adapted Proctor et al.’s conceptual model of implementation evaluation to show the relationships among factors that influence variability in success of quality improvement of colonoscopy (Fig. 1) [36, 37]. Aim #1 will explore the relative effect of two strategies to implement patient-level EBPs on quality outcomes. Aim #2 will assess aspects of endoscopy settings (i.e., perceptions of the evidence, the quality and structure of the relationship between physician and implementers) that influence implementation, patient, and colonoscopy quality outcomes in endoscopy settings.

#### Aim #1

Compare the effect of physician education versus physician education plus a staff implementation toolkit on staff adoption of evidence-based practices and colonoscopy quality outcomes (i.e., adequacy of bowel preparation, adenoma detection).

To accomplish aim #1, we will compare change in colonoscopy quality outcomes from before to after implementation of interventions for the two study groups: a) overall and b) Medicaid versus other insurance using administrative and medical record data with interrupted time series analysis.

### Settings and subjects

This study will be conducted with a convenience sample of six endoscopy settings. Our study is highly pragmatic with regard to eligibility. We will invite all 70 physicians that perform outpatient colonoscopy, regardless of their specialty (i.e., gastroenterology, surgery), and all of their staff that provide bowel preparation education to patients before outpatient colonoscopy. All patients scheduled for outpatient colonoscopy will be included, regardless of whether they are scheduled for a screening or diagnostic procedure. The PRECIS diagram illustrated in Fig. 2 reflects the extent to which each indicator of the study was pragmatic versus explanatory. Table 1 explains the PRECIS diagram by providing an assessment of each PRECIS domain for this study [38]. Our strategic partners will facilitate recruitment of physicians by co-signing recruitment letters and, if recruitment challenges occurs, by sending emails, calling physicians, and introducing the study at department meetings. Based on previous experience with physician recruitment to studies, we anticipate participation from at least 80 % of eligible physicians (70*0.80 = 56 physicians) and that each physician will have at least two staff that provide education for bowel preparation (56*2 = *n* = 112 staff). To minimize the potential for diffusion of treatment to our comparison group, we will assign physicians’ staff either to usual care or to receive the implementation toolkit. Physicians in both study groups will receive education. Assignment will be based on baseline adequacy of bowel preparation, balance of patient units and structure of physician-staff relationship. Over 10,000 outpatient colonoscopies per year are performed in our sample. Overall, 23 % of patients are covered by Medicaid. We anticipate inclusion of more than 10,000 patients in the study (20,000 over 2 years*15/24 months observation = 12,500*0.80 minimum physician participation = 10,000 total, >600 per month).

**Fig. 2 Fig2:**
[figure not shown]
PRECIS diagram of the pragmatic-explanatory continuum for the STIC study. The study becomes more pragmatic (and less explanatory) as each indicator point moves away from the central “E”

**Table 1 Tab1:** PRECIS assessment of the STIC study

PRECIS domains	Assessment of domain
Participant eligibility criteria	Eligible participants will include all physicians performing outpatient colonoscopy regardless of specialty, all staff providing bowel preparation education to patients before outpatient colonoscopy, and all patients scheduled for outpatient colonoscopy regardless of whether they are scheduled for a screening or diagnostic procedure.
Experimental intervention—flexibility	The experimental condition will allow for flexibility in the timing of staff delivering the intervention to patients so that the EBPs are integrated into existing processes as seamlessly as possible. However, staff may be provided with recommendations for the timing of intervention delivery to patients.
Experimental intervention—practitioner expertise	All physicians and staff members will be involved regardless of specialization, level of training, or expertise.
Comparison intervention(s)—flexibility	Physicians will receive an education module, but physicians’ staff members will be assigned to usual practice.
Comparison intervention(s)—practitioner expertise	All physicians and staff members will be involved regardless of specialization, level of training, or expertise.
Follow-up intensity	To boost the response rate above, initial mailings will include contacts from our strategic partners, and study staff will follow up weekly with email reminders and phone calls to non-respondents. After enrollment, no contact is made with physicians or staff.
Primary trial outcome	Primary outcomes will include both an intermediate implementation outcome (i.e., EBP adoption) and more long-range clinical outcomes (i.e., bowel preparation, adenoma detection). The outcomes, particularly the clinical outcomes, are well-specified, clinically meaningful, and assessed under usual conditions.
Participant compliance with intervention	Physician participation in the education module and provision of staff names, as well as staff participation rates for each component of the toolkit (i.e., education module, website, ordering materials, brief consultation) will be measured through Google Analytics and Qualtrics primarily for descriptive purposes and to inform improvement of the toolkit in future studies. No other compliance-improving strategies will be applied in this study.
Practitioner adherence to study protocol	The provision of teach-back and low-literacy education to patients will be measured and assessed but not fed back to staff or physicians during the course of the study. No ongoing data feedback or other adherence-improving strategies will be applied in this study.
Analysis of primary outcome	The segmented regression analysis of interrupted time series data (SRAITSD) will maximize external validity by informing the generalizability of effects across endoscopy settings and insurance strata.

### Delivery of patient interventions

We will allow for flexibility in the timing of staff delivering the intervention to patients so that the EBPs are integrated into existing processes as seamless as possible. However, when relevant during consultations (e.g., staff seeking advice), we will provide staff with recommendations for the timing of intervention delivery to patients. We will recommend that clinical staff mail the instructions for bowel preparation with an appointment reminder approximately 2 weeks prior to the procedure and call patients to use the teach-back method 1 week prior to the procedure.

### Implementation strategies

The primary aim of this study is to test the additive effect of physician education plus an implementation toolkit (compared to physician education alone) for endoscopy staff providing pre-colonoscopy bowel preparation education to patients on colonoscopy quality outcomes (i.e., adequacy of bowel preparation, adenoma detection). The implementation toolkit consists of four components: 1) *staff education module* including clinical goals for colonoscopy quality for adequacy of bowel preparation, adenoma detection, and cecal intubation, 2) *staff support website*, including information on the EBPs of split-dosing, teach-back, and low-literacy education, 3) *patient education materials*, including a 5-month supply of printed patient education brochures tailored to their practice and bowel preparation of their choice, plus a laminated pocket card and poster to remind and support staff to use teach-back, and 4) *brief consultation* with study staff to identify how EBPs can be integrated into existing workflow. The comparison group will receive the physician education module, but not the staff implementation toolkit.

### Measures

The Center for Clinical Excellence at BJC will obtain all data required for aim #1 from clinical and administrative systems at the endoscopy settings. The primary outcomes for aim #1 are adoption of EBPs, adequacy of bowel preparation, and adenoma detection. We will measure adoption of the EBPs (i.e., split-dosing, use of low-literacy education materials, teach-back) using a structured survey administered to staff and patients at baseline and follow-up. Sample questions on adoption will assess whether staff asked patients to “take half of the bowel preparation medication” (the day before/the morning of the test), with response options including “No,” “Yes,” and “I don’t know/Not applicable.” Questions will also be asked about whether or not staff provided the recommended low-literacy paper instructions and whether or not staff asked patients to “repeat instructions for bowel preparation in their own words.” Both clinical outcomes (adequacy of bowel preparation, adenoma detection) are standard elements of colonoscopy reports [10], and earlier research suggests that these data are routinely recorded in electronic records [39]. Bowel preparation is commonly described using the Aronchick scale (Kappa ICC 0.77) [40] as excellent, good, fair, or poor. Excellent or good ratings are considered adequate [5, 39]. Excellent refers to no or minimal solid stool and only small amounts of clear fluid requiring suctioning. Good refers to no or minimal solid stool with large amounts of clear fluid requiring suctioning. Fair refers to collections of semisolid debris that are cleared with difficulty. Poor refers to solid or semisolid debris that cannot be effectively cleared. We will also capture information about factors that are associated with adequacy of bowel preparation and adenoma detection including characteristics of the patient (age, gender, type of insurance, co-morbid conditions (i.e., history of constipation, diabetes), body mass index, use of narcotic medications) [41], primary language [14], and procedure (i.e., physician specialty, type of bowel preparation, indication for procedure, date of procedure [8]).

### Analysis

To assess change in clinical outcomes, we will use segmented regression analysis of interrupted time series data (SRAITSD). SRAITSD is an excellent analysis method for pragmatic studies because it minimizes threats to internal validity while maximizing external validity. For our application, individual patient outcomes are aggregated into proportion of adequate bowel preparation or proportion with adenoma detection in 2-week intervals, the time representing our unit of analysis. A sequence of the proportions over time generates time series data, with segments separated by two different interventions (i.e., comparative effectiveness and a replication study). The observation period for the time series analysis (Table 2) consists of three segments: baseline, comparative-effectiveness intervention, and replication study. Each segment is ~5 months in length. Two parameters define each segment of a time series: level and trend (see Additional file 1 for additional information on the analytic model) [42]. This model can be fit and tested using SAS software. We have a sufficient number of observations per segment (10 observations) and individual patient outcomes per observation (>100 units) for robust estimates of change in level and trend for outcomes [42, 43].

**Table 2 Tab2:** Interrupted time series study design—15-month observation period

Segments	Baseline			Comparative-effectiveness				Replication			
Group 1	O_1_	…	O_10_	X_1_	O_11_	…	O_20_	X_1_X_2_	O_21_	…	O_30_
Group 2	O_1_	…	O_10_	X_1_X_2_	O_11_	…	…	…	…	…	O_30_

*Note*: Each observation represents a 2-week interval. X1 = physician education, *X*2 = physician education plus staff training and support

To test intervention effects in each group, we first examine the plots of 2-week proportions over time. Then, we will fit the model separately in each group. β2 and β3 are the change in level and in trend of outcome, respectively, due to the comparative-effectiveness intervention. β4 and β5, which only apply to group 1, are the change in level and in trend of outcome, respectively, due to the replication study beyond the comparative-effectiveness intervention. For each group, statistical significance of these changes can be tested using the ratios of these regression coefficients to their estimated standard errors (*p* value). Because our study adopts a parallel design, we can also examine the statistical significance of the difference in these changes across groups by computing the difference in the regression coefficients divided by a standard error of the coefficient difference (*p* value), which can be easily obtained from standard errors of the regression coefficients in two separate models. A statistically significant (*p* < 0.05) difference in change in the level of outcome for group 1 versus group 2 will inform us about the comparative effectiveness of the physician education versus the physician education *plus* implementation toolkit. Alternatively, a statistically significant (*p* < 0.05) difference in trends of outcomes for group 1 versus group 2 will inform us about potential threats to validity due to outside events or program drift that occurs when fidelity to implementation protocols weaken over time. Finally, a statistically significant (*p* < 0.05) difference in the level of outcomes for group 1 in segment 2 versus group 1 in segment 3 will inform us about the generalizability of the comparative-effectiveness study effects across endoscopy settings. In order to examine modifying intervention effect by insurance status, we will stratify our study subjects by Medicaid versus other insurance status. Therefore, we will have 4 time series—two groups by two insurance strata. These series have the same time definition and the same segments, so the regression coefficients have the same interpretation. We will fit SRAITSD to each of the 4 time series and compare the relevant regression coefficients between Medicaid versus other insurance.

To assess the extent to which the implementation toolkit influenced adoption of EBPs over time, we will model adoption at follow-up as a function of study group assignment, controlling for the baseline measure of adoption. We will assess adoption for each EBP (i.e., split-dosing, low-literacy education, teach-back) separately and use separate statistical models for adoption measured from the perspective of the following: 1) staff, 2) physicians, and 3) patients. The regression coefficient for study group assignment will quantify the effect of different approaches on the outcome.

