### Analysis

If we find group-level effects, then we will dichotomize the readiness to change variables at mid-point (high, low) for the sample and analyze readiness to change at the physician-team level. We will examine the distribution of responses to the patient-experience survey for respondents overall and stratified by attendance. Our primary analysis for aim #2 will examine associations between each implementation and patient outcome and readiness to change using linear or logistic generalized estimating equations, depending on the distribution of the outcome, adjusted for patient and procedure characteristics. All analyses will be performed using SAS version 9.2. In addition, we will summarize data from aim #2 as six endoscopy setting case studies based on variability of clinical quality outcomes (aim #1) [46]. If we identify significant relationships between aspects of readiness to change and implementation, patient, or colonoscopy quality outcomes, then we will develop plans to analyze the patterns of these relations in a subsequent study that will be powered to address questions about pathways to readiness to change.

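### The aim #1 between-group test has no team-level replication and no covariance between series, so its 5% level is not controlled, in either direction

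*Protocol article*

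**What the plan says.** All references are to the protocol article, Methods/Design.

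- **Unit of assignment** (Settings and subjects): "we will assign physicians’ staff either to usual care or to receive the implementation toolkit". The basis given is baseline adequacy, balance of patient units and the physician-staff structure; randomisation is not mentioned. The article expects 56 physicians from six settings.
- **Unit of analysis** (Aim #1, Analysis): "individual patient outcomes are aggregated into proportion of adequate bowel preparation or proportion with adenoma detection in 2-week intervals", with time as the analysis unit. Table 2 shows 30 intervals, and both groups are interrupted after interval 10.
- **Fitting**: "Then, we will fit the model separately in each group". The two models differ, because the replication terms are described as "β4 and β5, which only apply to group 1".
- **Between-group test**: "A statistically significant (*p* < 0.05) difference in change in the level of outcome for group 1 versus group 2 will inform us" about comparative effectiveness. The standard error of the coefficient difference is one "which can be easily obtained from standard errors of the regression coefficients in two separate models".
- **Insurance**: four series (group by insurance) are fitted one by one and their coefficients compared.
- **Covariates** (Aim #1, Measures): "We will also capture information about factors that are associated with adequacy of bowel preparation and adenoma detection including characteristics of the patient". The procedure's indication and type of preparation are also listed.
- **Aim #2, Analysis**, by contrast, relates outcomes to readiness "using linear or logistic generalized estimating equations, depending on the distribution of the outcome, adjusted for patient and procedure characteristics".

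Further detail of the aim #1 model is left to Additional file 1, which is not at hand.

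**The concern.** The toolkit acts through the staff of each physician, and delivery is deliberately flexible. Uneven uptake is to be expected: the Background itself cites a median success rate of 33% for complex change initiatives. If teams shift by different amounts at interval 11, the group's mean shift carries that variation. A single pooled series shows it only as part of one step, never as scatter around the fitted line. The residuals, and so the standard error, then reflect mainly sampling noise within the series, and the test rejects too often.

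A second feature works the other way. Both groups live through the same calendar intervals, so disturbances common to both largely cancel in the difference. Adding the variances of two separate models counts them twice, and the test then rejects too rarely. The same omission affects Medicaid versus other insurance, where both series can come from the same physicians.

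At stake is the p value for comparative effectiveness, which is the primary question on the clinical outcomes.

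**Working it through.** **1. The article's own figures.** 20,000 × 15/24 × 0.80 = 10,000 patients; 10,000/15 = 667 per month; 10,000/30/2 = 167 per interval per group. These agree with the stated totals of 10,000, more than 600 and more than 100. Per team: 10,000/56/30 ≈ 6 patients per interval. The Medicaid series would hold about 0.23 × 167 = 38 per interval per group. No ICC, team-by-period variance or power calculation is given, so there is no test figure to reproduce.

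**2. Assumptions.** Adequacy is 70% (the Background says inadequacy can exceed 30%), with 80% as an alternative. Teams split 28:28 with equal volumes. The test is two-sided with critical value 1.96. All SDs of shifts and shocks below are assumed.

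**3. Standard error of the level change β2 from binomial noise.** SE = √[p(1−p)/167] × √v, where v is the diagonal element of (X′X)⁻¹ for β2 over 30 intervals. v = 0.812 for group 1 (six terms) and 0.561 for group 2 (four terms), counting time since interruption from 1.

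- 70%: 3.55 × 0.901 = 3.2 points (group 1); 3.55 × 0.749 = 2.7 points (group 2).
- 80%: 3.10 × 0.901 = 2.8 points; 3.10 × 0.749 = 2.3 points.
- Planned SE of the difference at 70%: √(3.20² + 2.66²) = 4.16 points.

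Counting time from 0 instead raises group 2's SE to 2.9 (70%) or 2.5 (80%).

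**4. Team-specific shifts, SD τ.** True variance = 4.16² + 2τ²/28; type I error = 2[1 − Φ(1.96 × 4.16/true SD)].

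- τ = 5: true SD 4.37, error 6.2%.
- τ = 10: true SD 4.94, error 9.9%.
- τ = 15: true SD 5.78, error 15.8%.

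**5. Shared interval shock, independent over time, SD = r × sampling SD.** The planned variance is proportional to (1 + r²)(0.812 + 0.561) = 1.373(1 + r²). In truth the shock enters only through the difference between the two models' weights, whose sum of squares is 0.251, so the true variance is proportional to 1.373 + 0.251r².

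- r = 0.5: √(1.716/1.436) = 1.09.
- r = 1.0: √(2.747/1.624) = 1.30.

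The separate-model SE is thus about 9-30% too large. Cancellation is incomplete because the two models have different terms.

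**6. Simulation of the planned test under the null** (group 1 with β0-β5, group 2 with β0-β3, least squares):

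| Scenario | Type I error |
|---|---|
| No clustering | 5.2% |
| Constant team differences, ICC 0.02 / 0.05 / 0.10 | 5.3% / 5.7% / 5.5% |
| Team shifts, SD 5 / 10 / 15 points | 6-7% / 10-11% / 15-16% |
| Independent shared shock, SD 2 / 3 / 4 points | 3.4% / about 2% / 1.1% |
| Autocorrelated (0.6) shared shock, SD 2 / 4 points | 5.0% / 3.6% |
| Shock SD 3 plus team shift SD 10 | about 4% |

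A comparison replicated at team level stayed at 4-6% throughout.

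**The case against.** The strongest reply is that no error has been shown. Constant differences between teams are absorbed by the level of each series and leave the test near 5%; only team-by-time variation inflates it, and the article gives no value for that. The omitted covariance works in the opposite direction, and in one combined scenario the two roughly offset at about 4%. All of this stands. A reader might infer that the p values are simply wrong, or that type I error is inflated; the documents support neither.

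A reader might also infer larger inflation from settings changing as blocks. With three settings per group and setting shifts of SD 5 points, simulation gives 17%. But the article assigns physicians' staff and nowhere says that whole settings go to one group. If settings contribute teams to both groups, such shifts partly cancel, so that figure is not relied on here.

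Finally, Additional file 1 might hold more of the model. It may well contain autocorrelation or covariate terms, so absence of case-mix adjustment cannot be claimed. Stable case-mix differences would in any case be absorbed by the level; only drift matters, and chiefly as bias. What such a file cannot do is put team replication into a single pooled series, or a covariance into a standard error taken from two separate models. Those features are stated in the article.

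**Conclusion.** The concern holds in a limited form. The stated between-group test uses no replication at the level at which staff are assigned and omits the covariance between series that share time or physicians. Its error rate is therefore not controlled. Over the assumed ranges it runs from about 1-2% (independent shared shocks of SD 3-4 points) to 15-16% (team shifts of SD 15 points), and stays near 5% if teams differ only by a constant. Which applies depends on variances the documents do not give. Possible offsetting of two errors of unknown size is not a reason to rely on the test when a team-level analysis holds its level across these scenarios. The analysis should be changed. Confidence is high about the structure of the test and moderate about the size and sign of the error.

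**What to change.** Take the between-group and between-insurance contrasts, with their standard errors, from one joint model of both groups on patient-level or team-by-interval data. It should contain:

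- common calendar-time effects;
- group-by-segment level and trend terms;
- an insurance interaction;
- clustering by physician team that allows team-specific change, through a random segment effect or team-robust standard errors with a small-sample correction;
- the covariates already listed under Measures, if the full model does not include them, as protection against case-mix that changes over time.

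Keep the separate-series fits and plots as descriptive or secondary. Both groups are interrupted at the same interval, so the within-group β2 and β3 tests are not identifiable under full interval effects.

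Cost: revised analysis wording and some programming, using data the article already plans to obtain. Intervals will be wider if teams differ in response, and the within-group tests lose primary status.
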